#### Follow-up

All patients will be followed in the hospital where they received treatment at the 16th week after random allocation and then at 3-month intervals in the first 2 years and at 6-month intervals for the next 3 years thereafter. Local or systemic recurrences and any AEs will be recorded. For the DCRT group, patients can be treated with salvage oesophagectomy if the disease does not reach complete remission at the 16th week follow-up. For the surgery group as well, patients can be treated with radiation or chemotherapy if R0 is impossible to reach or there is local recurrence at the 16th week of follow-up.

QoL will be evaluated in all patients using the Quality of Life Questionnaire-Core 30 (QLQ-C30 version 3.0, in Chinese) and the supplemental Quality of Life-Oesophageal Module 18 Questionnaire (QLQ-ES18, in Chinese) for patients with EC, both of which were developed by the European Organisation for Research and Treatment of Cancer (EORTC). For this evaluation, each patient will be visited in person during hospitalisation 1 week before and 1 week after surgery and contacted by telephone at 12 and 24 weeks postoperatively (Fig. 2) [17].

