**Methods/design:**

One hundred ninety-six patients with T1bN + M0 or T2-4aN0-2 M0 oesophageal squamous cell cancer will be randomised to the DCRT group or the surgery group. In the DCRT group, patients will be given intensity-modulated radiation therapy (IMRT) with 50 Gy/25 fractions and basic chemotherapy with 5-fluorouracil regimens. In the surgery group, patients will receive neoadjuvant chemoradiotherapy (NCRT) and standard oesophagectomy. Five years of follow-up will be scheduled for patients. The primary endpoints are 2-year/5-year overall survival; the secondary endpoints are 2-year/5-year progression-free survival, treatment-related adverse events and the patients’ quality of life. The main evaluation methods include oesophagoscopy, endoscopic ultrasonography and biopsy, oesophageal barium meal, computed tomography, positron emission tomography-computed tomography, blood tests and questionnaires.

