#### Chemoradiotherapy

##### Radiotherapy

Intensity-modulated radiation therapy (IMRT) will be performed for patients in the DCRT group with 50 Gy/25 F and in the surgery group with 42 Gy/21 F for NCRT, at 2 Gy/day, five times/week, until disease progression or unacceptable toxicity is found. The dosage for the individual patients will be governed by the dose constraints of the normal organs. The target volume length includes 5 cm on each side of the imaged visible tumour and malignant nodes. Radiotherapy will be delivered in two consecutive phases. Phase I starts with anterior-posterior opposing portals to 30 Gy, while phase II will be given with three fields to another 20 Gy (or 12 Gy in the surgery group for NCRT), which is subject to the limiting radiation dose of the heart, lung and spinal cord.

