#### Outcome measures

The primary outcome measures are 2-year/5-year overall survival (OS). The secondary outcomes are 2-year/5-year disease-free survival (DFS), treatment-related AEs and QoL. The recurrence of the disease is defined as either endoscopic recurrence confirmed with biopsy or distant metastasis. The operative mortality is defined as an in-hospital death within 30 days of the perioperative period.

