### Monitoring

#### Collecting, assessing, reporting and managing adverse events

The most common side effects of CRT are myelosuppression, oral mucositis, hand-foot syndrome and peripheral neuritis. More severe side effects are rare. Information about solicited and spontaneously reported AEs will be sought from all participants during telephone reviews by the trial General Practitioner/General Investigator (GP). If a participant reports an AE, the trial GP will determine appropriate action, which may include dose alteration or withdrawal. If an AE is identified as more serious than grade 4, the trial GP will forward this information immediately to the Principal Investigator and Data Safety Monitoring Board. All of the serious AEs (SAEs), suspected adverse reactions and serious suspected unexpected adverse reactions will be recorded immediately in the source documents and on the AE case report form. Each event will be followed until resolution or stabilisation or until it has been determined that the study treatment is not causal. SAEs still ongoing at the end of the study will be followed up to determine final outcome. Any SAE that occurs after the study will be recorded and reported immediately and considered to be possibly related to the study treatment. Economic compensation will be provided by the trial sponsor to those who suffer harm from the trial participation.

For the data monitoring of the QoL outcome, firstly, some measures will be taken to prevent and reduce missing data by enhancing investigator training, communication, patient education and data monitoring. Secondly, we will confirm the causes of missing data case by case and record them in detail. Finally, suitable missing data handling methods such as last observation carried forward (LOCF) or multiple imputation (MI) will be performed.

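### QoL is to be assessed in every patient, but every stated assessment time counts from an operation that the DCRT arm is not planned to have

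*Protocol article*

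**What the plan says.** The Outcome measures section makes QoL part of the two-arm comparison: "The secondary outcomes are 2-year/5-year disease-free survival (DFS), treatment-related AEs and QoL". The Follow-up section gives its scope, "QoL will be evaluated in all patients", and names two EORTC questionnaires, the QLQ-C30 and the oesophageal module. The timing comes in the next sentence: "each patient will be visited in person during hospitalisation 1 week before and 1 week after surgery and contacted by telephone". The telephone part of that sentence reads in full "contacted by telephone at 12 and 24 weeks postoperatively", and it refers to Fig. 2 for the schedule.

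On treatment order, the Abstract says: "In the surgery group, patients will receive neoadjuvant chemoradiotherapy (NCRT) and standard oesophagectomy". The Radiotherapy section gives the pre-operative course as "in the surgery group with 42 Gy/21 F for NCRT, at 2 Gy/day, five times/week". For the DCRT group, the Follow-up section mentions surgery only as optional salvage when complete remission has not been reached at week 16. Clinical visits in the same section are counted from random allocation: week 16, then three-monthly in the first 2 years and six-monthly for the next 3.

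The Recruitment section has participants complete baseline measures before allocation, without saying which. On missing QoL data, the section on collecting and managing adverse events says: "suitable missing data handling methods such as last observation carried forward (LOCF) or multiple imputation (MI) will be performed".

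**The concern.** The text states one QoL schedule and applies it to every patient, but ties it to an event that is planned in only one arm. Followed literally, it gives a DCRT patient no date on which to complete a questionnaire. It also gives the surgery arm no stated value from before treatment.

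A randomised comparison of QoL needs scores at corresponding times since randomisation and, preferably, a pre-treatment score to adjust for. Here the clinical visits have that origin and the QoL assessments do not. What is at stake is whether the secondary QoL comparison can be made at all. No later analysis plan can recover questionnaires that were not collected, and neither LOCF nor multiple imputation can fill times that were never defined.

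**Working it through.** The plan gives no figure for QoL, so there is none to reproduce. The check sets the stated times against each arm's treatment path.

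**Inputs from the article**
- 196 participants (Patients section), allocated 1:1 (Randomisation section).
- NCRT radiotherapy: 21 fractions, five a week (Radiotherapy section).
- Pilot complete-response rates in the DCRT regimens: 50%, 48.6% and 48% of 24, 37 and 25 patients (Discussion).

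**Assumption.** The interval from the end of NCRT to surgery is not stated. I take 4 to 8 weeks for illustration only.

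**Step 1: surgery arm.** NCRT radiotherapy lasts 21/5 = 4.2 weeks. Surgery then falls at 4.2 + 4 = 8.2 to 4.2 + 8 = 12.2 weeks after NCRT starts.

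| Stated QoL time | Surgery arm, weeks after NCRT starts | DCRT without salvage surgery |
|---|---|---|
| 1 week before surgery | 7.2 to 11.2 | no date |
| 1 week after surgery | 9.2 to 13.2 | no date |
| 12 weeks after surgery | 20.2 to 24.2 | no date |
| 24 weeks after surgery | 32.2 to 36.2 | no date |

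The interval moves the dates but not the conclusion. Because NCRT precedes the operation, none of the four stated times is a planned pre-treatment assessment.

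**Step 2: DCRT arm.** Half of 196 is 98 patients. The pilot rates correspond to 12/24, 18/37 and 12/25, so (12 + 18 + 12)/86 = 42/86 = 49%. If that rate carries over, and if pilot complete response is read as complete remission at week 16, about 0.49 × 98 = 48 patients would not meet the salvage condition. None of the four dates would exist for them. The other 50 or so could have salvage surgery, but it is optional.

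**Step 3: could salvage surgery serve as the DCRT anchor?** No. It would select patients who had not reached complete remission, and their first assessment would come from about week 16 onward. The DCRT sample would be chosen by treatment outcome, while the surgery arm would be measured around a planned operation.

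**Step 4: what a shared visit would measure.** If treatment starts at allocation (assumed), the week-16 visit falls 16 − 12.2 = 3.8 to 16 − 8.2 = 7.8 weeks after surgery. It is a valid common time, but for the surgery arm it reflects early recovery. Later common visits are therefore needed too.

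**Step 5: LOCF.** If a patient misses the 12-week call, the score carried forward is the one from 1 week after oesophagectomy. If only the 24-week call is missed, it is the 12-week score. Either can misstate later QoL. The shift in an arm mean equals the share missing times the average gap between the carried score and the true later score. The article gives neither quantity.

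**The case against.** The strongest reply is that the timing sentence points to Fig. 2, whose title covers assessments and which was not available here. It may give DCRT times or a pre-treatment questionnaire. This stands as a limit: a reader might infer that DCRT patients have no scheduled QoL at all, but only the prose supports that. It does not remove the point, because a figure with DCRT times would conflict with a sentence that applies the surgical schedule to each patient.

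Second, the pre-allocation baseline measures might include QoL. That also stands. One cannot say that QoL collection in the surgery arm definitely begins after NCRT, only that the stated schedule does and that QoL is not named at baseline. A baseline score would still leave the arms without common later times.

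Third, LOCF is one of two examples beside multiple imputation, and the choice may be settled in an analysis plan not shown. A reader might infer that LOCF is the planned method, that it would bias the surgery arm downward, or that scores would be filled in after death. The article supports none of these. An early post-operative low carried forward would lower the surgery mean, whereas carrying a score past deterioration would raise it. One could assume 10% to 30% missing and a 10 to 30 point recovery and obtain 0.10 × 10 = 1 to 0.30 × 30 = 9 points. Both inputs are invented, and the range requires the 1-week score always to be the one carried.

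Finally, the article does not present QoL as a main reason to prefer DCRT. It is listed as a secondary endpoint, and the point needs no more than that.

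**Conclusion.** The point holds for the prose. QoL is required in all patients, yet none of the four stated times is defined for a DCRT patient without salvage surgery, and none is a planned pre-treatment assessment in the surgery arm. The between-arm comparison therefore has no common time origin as written. This is a stated rule that cannot work for one arm, not a detail left to a fuller document.

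Up to 98 of 196 participants are affected. About 48 of them would have no route to any of the four dates if the pilot response rate carries over. The 4-to-8-week interval is illustrative and the conclusion does not rest on it. The finding is conditional on Fig. 2 and on the content of the baseline measures, neither of which could be seen.

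LOCF is a secondary weakness whose direction and size the document does not establish. Severity is should-fix: QoL is a secondary endpoint, and the overall survival analysis is untouched.

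**What to change.** - Name the QLQ-C30 and the oesophageal module among the baseline measures completed before allocation, so that both arms have a pre-treatment score.
- Schedule both questionnaires in both arms at common times counted from randomisation: the existing week-16 visit and chosen later three-monthly visits.
- Keep the peri-operative and post-operative assessments as descriptive data for the surgery arm.
- Base the between-arm comparison on the common times, adjusted for pre-treatment QoL.
- Remove LOCF as an option for the main QoL analysis and prespecify one method.
- Reconcile the Follow-up text with Fig. 2 if the figure gives other times.

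The cost is a short amendment and a few more questionnaires at visits that already take place. Recruitment began in April 2017 and may run to December 2020, so the change should be made soon. If QoL was not among the baseline measures, pre-treatment scores for patients already treated cannot be recovered, and the report should say how many patients lack one.

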**Fig. 2 Fig2:**
[figure not shown]
Schedule of enrolment, interventions and assessments

### Data management

This trial will be conducted in accordance with International Conference on Harmonisation (ICH) Guidelines for Good Clinical Research Practice and relevant local ethical regulations. Study data will be collected and managed using a regulatory approved electronic data capture system.

Data quality will be assured through range checks for data values. Integrity of trial data will be monitored by regularly scrutinising data for omissions and errors. In order to protect confidentiality before, during and after the trial, personal information about potential and enrolled participants will remain secure in a locked research office at the First Affiliated Hospital of HUST. Study data will be retained, securely password protected, for a minimum of 15 years from completion. Details of data management procedures can be found in the protocol.

### Data analyses

The primary method of analysis will be provision of descriptive statistics characterising key features, such as recruitment rate (number of patients approached, number consenting to participate and number eligible to be randomised), as well as frequencies and proportions of missing data and participant attrition, during both intervention and follow-up periods every 3 months.

### Sample size estimation and statistical analysis

Sample size calculation is based on the 5-year OS rates: 29.4% in patients treated with oesophagectomy and 50% in the DCRT group [18]. We used the log-rank test to compare the survival rate difference between the surgery and DCRT group. We defined α as 0.05 and β as 0.2. We supposed that the rate of loss to follow-up per year is 2.5% and 12.5% in 5 years. A sample size of 96 patients was determined to be required for each group.

The primary and secondary outcome measures will be compared using Student’s *t* test for the normally distributed data and the Mann-Whitney *U* test for the nonparametric data. For the data in proportions, a chi-squared test or Fisher’s exact test (if one of the expected values is less than 5) will be used. The provision of a 95% confidence interval will be calculated with the relative risk for cancer recurrence, morbidities and mortalities related to each therapy. We will use the Kaplan-Meier curve to represent the probability of survival within 2 years and 5 years after the initial diagnosis, and compare the two groups using the log-rank test. A value of *p* < 0.05 is considered to be statistically significant. The statistical analysis will be performed with the SPSS software (version 13.0; SPSS Inc., Chicago, IL, USA).

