Concurrent chemoradiotherapy (CRT) as a neoadjuvant therapy has preferable clinical efficacy and has become the standard treatment for local advanced EC with recognised guidelines [10–12]. Compared with chemotherapy or radiation alone, CRT has outstanding advantages. Not only does it achieve a higher rate of complete pathologic regression of oesophageal tumours, but it is also associated with a significant survival benefit [12]. A complete tumour response was frequently observed after neoadjuvant CRT (NCRT), and this has prompted investigations on the role of definitive concurrent chemoradiotherapy (DCRT) in locally advanced oesophageal carcinoma. However, most of those studies came from western, developed countries, and the majority of patients had adenocarcinomas. Different cell pathologies of the tumours could influence the clinical outcome following the same treatment strategy. In recent studies, neoadjuvant or adjuvant chemotherapy was associated with survival benefits in patients suffering from adenocarcinomas of the oesophagus. A prospective clinical study from Hong Kong University investigated the efficacy of CRT (three-dimensional conformal radiation therapy (3DCRT) in combination with two cycles of 5-fluorouracil (5-FU) and cisplatin) compared with surgery in oesophageal squamous cell cancer. Though this trial had shown no significant difference in the 2-year overall survival (OS) between the two study arms, a superior 5-year OS was found in the CRT arm, but with no statistical significance [13, 14].

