#### Patients

A total of 196 ESCC patients with T1bN + M0 or T2-4aN0-2 M0 will be randomised to the CRT group or the surgery group.

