Researchers from Hong Kong University initiated an excellent prospective clinical trial to compare the long-term outcomes between DCRT and surgery for ESCC patients. In this study, the overall 5-year survival favours CRT, but the difference did not reach statistical significance (surgery 29.4% and CRT 50%, *p* = 0.147) [13, 14]. The intervention of chemoradiotherapy used in this study is cisplatin 60 mg/m^2^ with hydration therapy given on days 1 and 22, whereas 5-FU is administered as a continuous infusion at 200 mg/m^2^/day from day 1 to day 42. Radiotherapy was delivered as three-dimensional conformal radiation therapy (3DCRT) with a total of 50–60 Gy given in 25–30 fractions over 5–6 weeks. It is inconvenient for patients to be administered 5-FU continuously for 42 days, while IMRT has been reported as more effective and tolerable than 3DCRT. Therefore, we designed this study to investigate the role of DCRT compared with NCRT followed by radical operation in patients with locally advanced ESCC in the highest incidence area worldwide using IMRT (50 Gy/25 F) and different chemotherapy regimens (capecitabine, Xelox, PF, randomised delivery). In the pilot trial, 86 patients finished 16 weeks of follow-up with at least these three regimens in the DCRT group (capecitabine:Xelox:PF = 24:37:25) [19, 20]. The incidences of grade 3–5 AE were 25%, 32.4% and 64% (*p* = 0.03) and the pathological complete response (pCR) rates were 50%, 48.6% and 48% in the three subgroups, respectively (*p* = 0.99). Additionally, objective response rates (ORRs) of 87.5% (21/24), 83.8% (31/37) and 100% (25/25), respectively (*p* = 0.133) were observed. No differences were seen in the complete response (CR) and ORR between the three subgroups. Therefore, it is worth exploring the roles of both the DCRT and single capecitabine in CRT in patients with advanced ESCC using a larger sample size.

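### The control-arm 5-year survival used for sizing (29.4%) comes from an arm described only as surgery, but this trial's control arm is NCRT plus oesophagectomy, so the stated 80% power is not established for the comparison being run

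*Protocol article*

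**What the plan says.** The section on sample size estimation and statistical analysis fixes the two survival rates: "Sample size calculation is based on the 5-year OS rates: 29.4% in patients treated with oesophagectomy and 50% in the DCRT group [18"]. It adds a log-rank test, α 0.05, β 0.2 and 12.5% loss over five years, and concludes: "A sample size of 96 patients was determined to be required for each group".

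The Discussion shows where the rates come from. Of the Hong Kong trial of definitive chemoradiotherapy (DCRT) against surgery, cited as [13, 14], it says that "the overall 5-year survival favours CRT, but the difference did not reach statistical significance (surgery 29.4% and CRT 50"%, and gives p = 0.147. Neither the Discussion nor the Background mentions neoadjuvant treatment in that trial's surgery arm.

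This trial's control arm is defined in the Abstract: "In the surgery group, patients will receive neoadjuvant chemoradiotherapy (NCRT) and standard oesophagectomy". The Randomisation section names the same arm, and the Radiotherapy section sets a planned NCRT dose for the surgery group.

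**The concern.** A power statement holds only for the event rates put into it. The control rate here describes one treatment and the trial's control arm receives another. The article does not say why a rate reported for surgery should apply after NCRT, and it gives no range. It does call neoadjuvant chemoradiotherapy the standard treatment for locally advanced disease and credits it with preferable efficacy (Background), so the two treatments cannot simply be taken as interchangeable.

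Overall survival is the primary endpoint. If control survival is above 29.4% while DCRT stays at 50%, the contrast shrinks and the chance of detecting it can fall well below 80%. A reader who relies on β = 0.2 would then misjudge how informative a non-significant result is.

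Two smaller faults sit in the same place. The rates are referenced to [18], which the Discussion uses for a different report, on regression after NCRT by histology. And two groups of 96 make 192, whereas the Patients section has "A total of 196 ESCC patients".

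**Working it through.** **Inputs from the article:** 5-year survival 29.4% (control) and 50% (DCRT); log-rank test; α 0.05; power 80%; loss 2.5% per year, 12.5% in five years; 96 per group; 196 in total. α is taken as two-sided, because that reproduces the stated size.

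**Reproducing 96 per group.**
- Proportional hazards: HR = ln 0.50 / ln 0.294 = 0.6931 / 1.2242 = 0.566.
- Freedman: events = (1.960 + 0.842)² × [(1 + HR)/(1 − HR)]² = 7.849 × (1.566/0.434)² ≈ 102.3.
- Mean 5-year death probability = 1 − (0.294 + 0.50)/2 = 0.603.
- Per arm before loss: 102.3 / 0.603 / 2 = 84.8.
- Loss added as × 1.125: 95.4, rounded up to **96**, the stated figure.
- With events rounded up to 103 and loss handled as ÷ 0.875: 103 / 0.603 / 2 = 85.4, then 97.6, rounded up to 98 per arm, or 196. This may be the origin of 196, but the article does not say so.

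The arithmetic is sound. What remains open is the control input.

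**Power at other rates.** The article gives no 5-year survival for NCRT plus surgery in squamous cancer, so every rate below other than 29.4% with 50% is an assumption. Schoenfeld: power = Φ(½ × √D × |ln HR| − 1.960), where D is the number of deaths, with 98 per arm and five years of planned follow-up. Loss is handled in two ways:
- Crude removal of 12.5%: D = 196 × 0.875 × (1 − mean 5-year survival).
- Exponential loss at 2.5% per year: per-arm death probability = λ/(λ + 0.025) × (1 − exp[−5(λ + 0.025)]), with λ = −ln(S)/5; D = 98 × the sum over the two arms.

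Example at the planned rates, crude: D = 171.5 × 0.603 = 103.4; ½ × √103.4 × 0.569 = 2.892; 2.892 − 1.960 = 0.932; power 82%.

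| Control | DCRT | HR | D (crude / exponential) | Power (crude / exponential) |
|---|---|---|---|---|
| 29.4% | 50% | 0.566 | 103.4 / 112.2 | 82% / 85% |
| 35% | 50% | 0.660 | 98.6 / 106.9 | 54% / 57% |
| 40% | 50% | 0.756 | 94.3 / 102.2 | 27% / 29% |
| 45% | 50% | 0.868 | 90.0 / 97.5 | 10% / 10% |
| 35% | 55% | 0.569 | 94.3 / 102.2 | 78% / 81% |

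By the same formulas, a control rate of 40% needs a DCRT rate of about 60–61% for 80% power. With 96 per arm instead of 98, power changes by about one percentage point or less.

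**The case against.** The tempting stronger reading is that NCRT improves survival, so 29.4% is too low and the trial is underpowered. A reader might rest this on the Background's remark about chemoradiotherapy that "it is also associated with a significant survival benefit [12"]. The article does not carry that reading. The comparison there is with chemotherapy or radiation alone, not with surgery alone. The Background adds that most of the studies were western and mainly in adenocarcinoma, and that pathology could alter the outcome. The Discussion reports less regression after NCRT in squamous cancer and calls long-term survival after either strategy unclear. The Background also puts 5-year survival after surgery alone at 10–20%, so 29.4% already lies above the article's own general range. None of this turns 29.4% into a rate for NCRT plus surgery, but it does prevent the conclusion that the rate is too low.

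Nor need the control rate move alone. The Discussion says IMRT is reported to be more effective than the technique of the source trial, so the authors may expect better DCRT survival too. At 35% against 55%, power is again close to 80%. This objection stands, and it is why both arms should be varied.

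A reader might also infer that a non-significant result will be taken as equivalence. The article plans no such inference; its stated question is whether DCRT benefits patients more than oesophagectomy.

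The wrong reference and the 192 against 196 are editorial and barely affect power. The randomised comparison and the log-rank test remain valid whatever rates were assumed. What survives all of this is the mismatch itself: a specific rate, carried over from a differently described treatment, with no justification.

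**Conclusion.** The point holds in a limited form. The 80% power was calculated for a control rate that the article attributes to the surgery arm of a surgery-versus-chemoradiotherapy trial. It is not established for NCRT plus surgery against DCRT. If NCRT happened to add nothing to control survival, the figure would be right only by coincidence.

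The direction and size of the error cannot be determined from the article. The calculations show only how sensitive the power is: with DCRT fixed at 50%, a rise of 5.6 points in the control rate, to 35%, takes power from 82–85% to 54–57%, and raising DCRT to 55% as well brings it back to 78–81%. These figures assume proportional hazards, exponential survival where partial follow-up is credited, five years of planned follow-up, a two-sided test, and rates that the article does not supply. Whether the source trial's surgery patients had any neoadjuvant treatment cannot be checked here; the article describes none.

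**What to change.** Rewrite the sample-size paragraph, leaving enrolment as it is:

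1. State that 29.4% comes from the surgery arm of the trial cited as [13, 14], and correct the reference to [18].
2. Either justify 29.4% as the expected 5-year survival after NCRT plus oesophagectomy in squamous cancer, or replace it with a rate for that treatment and name its source.
3. In place of the single 80%, give power for the fixed sample over a range of control and DCRT rates, varying both arms, with the detectable difference at each control rate. State the sidedness of α and how loss is handled.
4. State one total: 2 × 96 = 192 or 2 × 98 = 196.

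The cost is one paragraph and a small table, with no extra patients and no change to conduct or analysis. The drawback is that the stated power may become less favourable.

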#### Recruitment

Recruitment will be from cancer centres of the First Affiliated Hospital of HUST, Anyang Tumour Hospital of HUST and Nanyang Centre Hospital, Henan province, China. Research staff will regularly check the inpatient - registry information system and identify any potentially eligible patients. They will liaise with an oncologist to ensure that the patient’s history and screening results are clear for study commencement. Eligible participants who present at the cancer centre when research staff are present will complete informed consent documentation after discussion with the oncologist, fill out baseline measures and then be randomly allocated to the DCRT group or the NCRT plus surgery group.

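### Quality-of-life scores are to be compared by an unadjusted two-sample test, which is valid but less precise than one adjusted for a pre-randomisation score, if that score is collected

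*Protocol article*

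**What the plan says.** The Outcome measures section lists QoL among the secondary outcomes. Under Follow-up, "QoL will be evaluated in all patients using the Quality of Life Questionnaire-Core 30" and the oesophageal module QLQ-ES18. The times given there are 1 week before surgery, 1 week after it, and 12 and 24 weeks postoperatively.

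The section Sample size estimation and statistical analysis fixes the method: "The primary and secondary outcome measures will be compared using Student’s" t test for normal data, with the Mann-Whitney test otherwise. Proportions go to a chi-squared or Fisher test, and survival goes to Kaplan-Meier curves and the log-rank test. The article names no baseline covariate, change score, ANCOVA or repeated-measures model. Its only further wording on the handling of QoL data is in the Monitoring section, which deals with missing data by last observation carried forward or multiple imputation.

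The Recruitment section describes consented patients who "fill out baseline measures and then be randomly allocated to the DCRT group or the NCRT plus surgery group". It does not say what the baseline measures are.

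**The concern.** Questionnaire scores are neither proportions nor survival times, so they fall to the t or Mann-Whitney sentence. A patient's score before treatment usually predicts part of the later score. A two-sample test on the follow-up score leaves that predictable part in the error variance, and a model with the baseline score as covariate removes it. The order of steps under Recruitment suggests that such a score may already be collected.

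What is at stake is the precision of the QoL comparison between an oesophagectomy strategy and a non-surgical one. The trial was sized for 5-year survival and no power is stated for QoL. Precision that costs almost nothing is therefore worth having.

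**Working it through.** **1. The plan's own figure.** The only sample size stated is for survival. Inputs: "29.4% in patients treated with oesophagectomy and 50% in the DCRT group" at 5 years, "We defined α as 0.05 and β as 0.2" (taken as two-sided), and "the rate of loss to follow-up per year is 2.5% and 12.5% in 5 years".

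- Hazard ratio = ln(0.5)/ln(0.294) = 0.566.
- Events by Freedman's formula: (1.960 + 0.842)² × [(1 + 0.566)/(1 − 0.566)]², which rounds up to 103.
- Mean 5-year death probability = 1 − (0.294 + 0.5)/2 = 0.603.
- Per group = 103/0.603/2 = 85.4.
- Allowing for loss: 85.4 × 1.125 = 96.1, or 85.4/0.875 = 97.6, which rounds up to 98.

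The first agrees with "A sample size of 96 patients was determined to be required for each group". The second gives 2 × 98 = 196, the total in the Patients section. Neither figure was derived for QoL.

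**2. Inputs for QoL.** The article gives no baseline-to-follow-up correlation (ρ), no QoL effect and no SD. All three are assumptions here. ρ runs from 0.3 to 0.7, the SD is set to 1, and the reference effect is the one that gives the unadjusted t test 80% power.

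**3. Effect of adjustment.** ANCOVA multiplies the residual variance by 1 − ρ². Starting from 80% unadjusted power, two-sided 0.05:

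Adjusted power = Φ[(1.960 + 0.842)/√(1 − ρ²) − 1.960]

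| ρ | 1 − ρ² | Unadjusted | Adjusted |
|---|---|---|---|
| 0.3 | 0.91 | 80% | 83.6% |
| 0.4 | 0.84 | 80% | 86.4% |
| 0.5 | 0.75 | 80% | 89.9% |
| 0.6 | 0.64 | 80% | 93.8% |
| 0.7 | 0.51 | 80% | 97.5% |

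The number per arm cancels from this comparison, so the table is the same for 96 or 98.

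**4. Dependence on the effect.** With ρ = 0.5 and 96 per arm, unadjusted power is Φ[d/√(2/96) − 1.960]. Adjusted power divides the first term by √0.75 = 0.866.

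| d (SD units) | Unadjusted | Adjusted | Gain (points) |
|---|---|---|---|
| 0.3 | 54.7% | 67.0% | 12.3 |
| 0.4 | 79.1% | 89.3% | 10.1 |
| 0.5 | 93.4% | 97.9% | 4.6 |

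Gains are taken before rounding.

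**5. Detectable difference.** With 98 per arm, all contributing a score, 80% power needs 2.802 × √(2/98) = 0.400 SD unadjusted. At ρ = 0.5 it needs 0.400 × 0.866 = 0.347 SD adjusted. Deaths and missing questionnaires would enlarge both.

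**6. Change scores.** The text does not say that the t test is run on change from baseline. If it were, the variance would be 2(1 − ρ) times that of the raw score, which is 1.0 times at ρ = 0.5. The shortfall against ANCOVA at ρ = 0.5 would be the same.

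**7. Which score could be the covariate.** The first QoL time under Follow-up is 1 week before surgery. That is after allocation and, in the surgery arm, after neoadjuvant chemoradiotherapy has started, so treatment may already have affected it. Only a score completed before randomisation will serve. The other times are also counted from surgery, and the text states no counterpart for the DCRT arm.

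**The case against.** The strongest objection is that the article documents no pre-randomisation QoL score. The Follow-up section lists none, and the Recruitment section does not name the questionnaires. Fig. 2, which might settle it, was not available for this check. If there is no such score, there is nothing to adjust for. This stands, and it makes the point conditional. The inference that the questionnaires are included is reasonable, because they are the only patient-completed instruments the article names, but it remains an inference.

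Second, the sentence on tests is generic, and covariates are often left to the analysis plan. This stands only in part. The article does not stay silent: it names the tests for secondary outcomes, and an analysis plan that followed it would run them unadjusted.

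Third, the size depends on an assumed correlation and an assumed effect, and the calculation covers the t test only. No gain has been computed for the Mann-Whitney test. This stands too.

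Two stronger readings are tempting. A reader might infer that chance imbalance in baseline scores biases the planned comparison, the more so because the Randomisation section mentions no stratification. The documents do not support that: allocation is random, and the unadjusted test's standard error already reflects chance imbalance. A reader might also infer that the plan gives up a fixed 10 points of power. The article fixes neither the correlation nor the QoL effect, and it does not confirm the covariate.

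**Conclusion.** The point holds as a conditional loss of precision on a secondary endpoint. The stated test is valid and unbiased under randomisation, and a baseline-adjusted analysis would be better if the score exists. From 80% unadjusted power, the gain is about 4 points at a correlation of 0.3, 10 at 0.5 and 18 at 0.7 (97.5 − 80 = 17.5). At a correlation of 0.5 it falls to about 5 points when unadjusted power is already about 93%. These figures rest on the questionnaires being completed before allocation, on the assumed correlation and effect, and on a two-sided 5% level. The survival endpoints and the sample size are not affected. This is a low-cost improvement worth making, not a flaw that undermines the trial.

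**What to change.** - In Sample size estimation and statistical analysis, replace the t or Mann-Whitney comparison for QLQ-C30 and QLQ-ES18 scores. Use ANCOVA, or a repeated-measures model, of the follow-up scores on arm, adjusted for the score completed before randomisation.
- In Recruitment, confirm that both questionnaires are among the baseline measures.
- State that the score taken 1 week before surgery is not the covariate, because it follows allocation and the start of neoadjuvant chemoradiotherapy.
- In Follow-up, define the QoL comparison at times counted from randomisation and common to both arms. Without this, a model of follow-up score on arm is not well defined, whatever the covariate.

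Cost: short wording changes in three sections, a little more analysis work, and simple imputation where a baseline score is missing. No visit is added for the baseline score if the questionnaires are already completed then. If they are not, they would have to be added there, and the adjustment could not draw on a real baseline score for patients already randomised.
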